# A Hospital-Wide Open-Label Cluster Crossover Pragmatic Comparative Effectiveness Randomized Trial Comparing Normal Saline to Ringer’s Lactate: Protocol and Statistical Analysis Plan of The FLUID Trial

**DOI:** 10.2196/51783

**Published:** 2023-10-06

**Keywords:** statistical analysis plan, fluid therapy, normal saline, Ringer’s lactate, cluster randomized trial, pragmatic, comparative effectiveness

## Abstract

**Background:**

Normal saline (NS) and Ringer’s lactate (RL) are the most common crystalloids given to hospitalized patients. Despite concern about possible harm associated with NS (eg, hyperchloremic metabolic acidosis, impaired kidney function, and death), few large multicenter randomized trials focused on critically ill patients have compared these fluids. Uncertainty exists about the effects of these fluids on clinically important outcomes across all hospitalized patients.

**Objective:**

The FLUID trial is a pragmatic, multicenter, 2×2 cluster crossover comparative effectiveness randomized trial that aims to evaluate the effectiveness of a hospital-wide policy that stocks either NS or RL as the main crystalloid fluid in 16 hospitals across Ontario, Canada.

**Methods:**

All hospitalized adult and pediatric patients (anticipated sample size 144,000 patients) with an incident admission to the hospital over the course of each study period will be included. Either NS or RL will be preferentially stocked throughout the hospital for 12 weeks before crossing to the alternate fluid for the subsequent 12 weeks. The primary outcome is a composite of death and hospital readmission within 90 days of hospitalization. Secondary outcomes include death, hospital readmission, dialysis, reoperation, postoperative reintubation, length of hospital stay, emergency department visits, and discharge to a facility other than home. All outcomes will be obtained from health administrative data, eliminating the need for individual case reports. The primary analysis will use cluster-level summaries to estimate cluster-average treatment effects.

**Results:**

The statistical analysis plan has been prepared “a priori” in advance of receipt of the trial data set from ICES and any analyses.

**Conclusions:**

We describe the protocol and statistical analysis plan for the evaluation of primary and secondary outcomes for the FLUID trial.

**Trial Registration:**

ClinicalTrials.gov NCT04512950; https://classic.clinicaltrials.gov/ct2/show/NCT04512950

**International Registered Report Identifier (IRRID):**

DERR1-10.2196/51783

## Introduction

Crystalloid resuscitation fluids, including normal saline (NS) and Ringer’s lactate (RL), are among the most common interventions administered in hospitalized patients [1,2]. These fluids may be used as a life-saving measure to re-establish hemodynamic stability, replace fluid losses, and maintain intravascular volume.

In observational studies, NS has been associated with acute renal injury as compared to RL and other balanced crystalloid fluids, hypothesized to be due to higher chloride concentration and resultant metabolic acidosis that can occur with NS administration [3-5]. However, RL and other balanced crystalloid fluids with buffers have the potential to cause metabolic alkalosis [6,7] and theoretically, cause arrhythmias, tetany, coma, and seizures [8-10]. The lactate in RL may accumulate in the setting of liver failure and may influence clinical diagnoses and clinical decision-making [11-13]. Moreover, RL has a lower osmolarity in comparison to NS; when administered rapidly in large volumes, RL theoretically reduces plasma osmolarity and increases the risk of edema formation [14], which raises potential concern for patients with cerebral edema.

In total, 2 large single-center multiple crossover trials conducted in the intensive care unit (ICU) and the emergency department (ED) among patients who did not require admission to the ICU, found that balanced crystalloid fluids as compared to NS were associated with lower major adverse kidney events at 30 days, which is a composite outcome of mortality, new renal replacement therapy, or persistent renal dysfunction [2,15]. In contrast, 2 large multicenter randomized trials (Balanced Solution versus Saline in Intensive Care Study [BASICS]; Plasma-Lyte 148 versus Saline [PLUS]) [16,17] examined the efficacy of NS as compared to a balanced crystalloid (RL and Plasma-Lyte 148 respectively) on the primary outcome 90-day mortality. Neither of these trials detected differences in 90-day mortality. In BASICS, the mortality rate was 22% versus 21.8%; and in PLUS, mortality was 27.2% versus 26.4% in patients receiving NS and RL, respectively. Renal function did not differ between the fluid groups in either trial, although the PLUS trial was stopped early due to recruitment challenges and insufficient funding during the pandemic. In a systematic review of 35,884 participants in 13 critical care trials published before January 2022, there were no detectable differences in renal function. In low-risk-of-bias trials, there was no significant difference in mortality for the NS as compared to the balanced crystalloid group (28.2% and 27.9% respectively; Relative Risk 0.96, 95% CI 0.91-1.01), nor renal function [15-28]. However, the authors concluded that there is a high probability that balanced crystalloids reduce death since the CIs ranged from a 9% relative reduction to a 1% relative increase in death.

Crystalloid fluids are administered to the majority of patients admitted to the hospital and continued throughout their hospital stay. To address ongoing uncertainty on this topic, and address this evidence gap about fluid administered outside the ED and ICU, we designed a cluster randomized crossover trial. Our objective was to compare a hospital-wide strategy to preferentially stock NS or RL as the main crystalloid resuscitation fluid, aiming to have all admitted patients receive the allocated crystalloid from the time they enter hospital to hospital discharge, evaluating the primary composite outcome of death or readmission to hospital in the first 90 days. The design of the FLUID trial is novel because it involves a pragmatic cluster randomized crossover design, a waiver of patient informed consent to include all hospitalized patients, hospital-based randomization, and the use of routinely collected electronic health administrative data for the description of baseline characteristics and all study outcomes. FLUID will generate data at low risk of bias, providing key evidence about the consequences of crystalloid fluid on clinically important outcomes, and informing patient care and health care policy. It will also provide insight into a novel approach to the conduct of large pragmatic clinical trials.

This manuscript describes the protocol and statistical analysis plan for the evaluation of primary and secondary outcomes for the FLUID trial.

## Methods

### Overview

The protocol and feasibility results for the FLUID pilot trial have been published [29,30]. The 4 pilot sites will be included in the analysis of the large trial as only feasibility outcomes have been previously reported and no major protocol changes were necessary following the pilot trial. The structure of this protocol and statistical analysis plan (version 1.0; March 29, 2023) follows the SPIRIT (Standard Protocol Items: Recommendations for Interventional Trials) Guidelines [31] (see Multimedia Appendix 1 and Table 1) and Guidelines for the Content of Statistical Analysis Plans in Clinical Trials (see Multimedia Appendix 2) [32]. The reporting of the trial results will follow the CONSORT (Consolidated Standards of Reporting Trials) Statement’s extension for Cluster Trials [33] and Randomized Crossover Trials [34], as applicable.

**Table 1 table1:** SPIRIT (Standard Protocol Items: Recommendations for Interventional Trials) table.

Study period										
Preallocation				Postallocation						
Time point		Enrollment (–t_1_)	Allocation (0)	Run-in (1 week)	Period 1 (12 weeks)	Wash-out (2 weeks)	Run-in (1 week)	Period 2 (12 weeks)	Wash-out (2 weeks)	Close-out
**Enrollment**										
	Eligibility screen	✓								
	Allocation		✓							
**Interventions**										
	Fluid A				✓			✓		
	Fluid B				✓			✓		
**Assessments**										
	Demographics	✓								
	Case mix group	✓								
	Type of surgical admission	✓								
	Surgical subgroup	✓								
	Severity of illness	✓								
	Comorbidities	✓								
	Primary outcome									✓
	Secondary outcomes									✓

### Trial Design

The study is a pragmatic, multicenter, 2×2 cluster crossover comparative effectiveness randomized trial. A completed PRECIS-2 table and wheel have been attached as Table S1 and Figure S1 in Multimedia Appendix 3. We defined clusters as hospital sites, allocated to one of two sequences in a 1:1 ratio. The interventions are a hospital-wide strategy of stocking predominantly NS (control) or RL (treatment) throughout the hospital. FLUID is an open-label trial as the cost of blinding the fluids is infeasible and prohibitively costly; this design is in keeping with a real-world evaluation of NS and RL whereby research is integrated into clinical care.

FLUID has two 15-week study periods. For each study period, week 1 will serve as a run-in, weeks 2-13 (12 weeks) as the study period during which all patients with index admissions to the study hospital will be included for analysis. Weeks 14 and 15 are the run-out period during which time the study fluid remains stocked in the hospital for use by patients admitted during weeks 2-13; however, new patients admitted during weeks 14 and 15 will not contribute to the analysis. After the 2-week run-out period, sites will have 1 week to switch out the study fluid and cross over to the period 2 study fluid. See Figure 1.

**Figure 1 figure1:**
[figure not shown]
FLUID trial study design.

### Trial Population

#### Cluster Screening and Eligibility

Inclusion criteria for participating clusters include (1) level II or III ICU capacity [35] and (2) the admission of at least 6000 patients per year to hospital. A list of included study sites will be included in the main trial report.

#### Patient Screening and Eligibility

All admitted patients to participating study sites for the first time (index hospital admission) over the duration of the study period will be included under a waiver of informed consent obtained from the research ethics committee; only neonatal patients (age <1 month) will be excluded as RL is not recommended for use in this population [36]. Patients readmitted to the hospital during study periods 1 or 2 and patients admitted during the run-in or run-out study periods will also be excluded. An index admission is defined as a patient admission with no prior hospital admission in the previous 90 days. CONSORT flow diagram of participant recruitment is presented in Figure 2.

**Figure 2 figure2:**
[figure not shown]
CONSORT (Consolidated Standards of Reporting Trials) flow diagram for participants.

#### Randomization

The order of treatment allocation for each hospital site (cluster) will be randomly assigned using computer-generated random numbers, using a permuted block design of length 2, at the coordinating center. The allocation sequence will be prepared by a statistician not familiar with the participating sites, which will be randomized in a 1:1 ratio. Half of the sites will be allocated to sequence 1 and begin the trial with NS as the control, while the other half will be allocated to sequence 2 and begin the trial with RL as the treatment. Each site will cross over to the other fluid after the 12-week study period. To control for period effects, while balancing logistical considerations, randomization will proceed in batches of 4 sites. The allocation sequence will be maintained on a password-protected computer and concealed from investigators until the next batch of sites have been enrolled and are ready to receive their allocation.

### Approach to Safety

No serious adverse events were reported to the coordinating center during the 4-center pilot trial. A Data and Safety Monitoring Committee conducted a review of the data from the 4-center pilot trial, reporting no reason to suspect harm resulting from either fluid. For the main trial, participating hospitals monitor serious adverse events via routinely scheduled meetings of safety committees or morbidity and mortality rounds. Site Principal Investigators report to the coordinating center any serious adverse event occurrence related to study fluid administration.

### Sample Size

A total of 16 hospital sites (including the 4 pilot sites) will yield data on approximately 144,000 hospital admissions. It required 12 sites in a 2-period cluster crossover trial over 6 months to achieve 80% power with a 2-sided α of 0.05 to detect a minimum clinically important absolute difference of 1% in the primary outcome in favor of RL, assuming a proportion of 0.16 in the NS condition, a within-period intracluster correlation coefficient of 0.006, a cluster autocorrelation coefficient of 0.95, and an average of 1500 patients per hospital per month [37]. These estimates were calculated from available routinely collected data for January 1 to December 31, 2013, for all eligible hospitals across the province of Ontario, Canada. Our calculations account for nonadherence based on pilot data (94% adherence NS, 80% RL). We added 2 clusters as an approximate small sample correction [38] and a further 2 to account for cluster size variation [38], for a final sample size of 16 sites.

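### The anticipated 144,000 assumes six full months of accrual, but the two 12-week inclusion windows give about 133,000 at the plan's own rate

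*Protocol article*

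**What the plan says.** The Sample Size section of the protocol article gives the total: "A total of 16 hospital sites (including the 4 pilot sites) will yield data on approximately 144,000 hospital admissions". Its inputs stand in the same paragraph: "an average of 1500 patients per hospital per month", and for duration and power, "It required 12 sites in a 2-period cluster crossover trial over 6 months to achieve 80% power". The rates come from routine Ontario data for the calendar year 2013. The abstract (Methods) carries the same total as "anticipated sample size 144,000 patients", there attached to patients with an incident admission.

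The Trial Design section fixes who is counted. Each study period has 15 weeks, of which only part accrues: "weeks 2-13 (12 weeks) as the study period during which all patients with index admissions to the study hospital will be included for analysis". On the run-out it adds that "new patients admitted during weeks 14 and 15 will not contribute to the analysis". Patient Screening and Eligibility confirms that run-in and run-out admissions are excluded, along with readmitted patients and neonates, and gives the unit: "An index admission is defined as a patient admission with no prior hospital admission in the previous 90 days".

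**The concern.** The total and the design use different accrual times. The total needs six full months per hospital, while the design accrues for 2 × 12 = 24 weeks, which is shorter than six calendar months. Either the headline size or the rate behind it is misstated. The unit also shifts: hospital admissions in one place, patients with an incident admission in the other.

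At stake are the accuracy of a stated sample size and the cluster-period size that goes into the power calculation. If the latter was taken as three full months, it is somewhat too large.

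**Working it through.** **Inputs from the article.** 16 sites; 1500 patients per hospital per month; 6 months; 12 counted weeks in each of two periods. For power: two-sided α 0.05, proportion 0.16 under NS, absolute difference 0.01, within-period ICC 0.006, cluster autocorrelation 0.95.

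**Step 1: reproduce the stated total.** Sites × rate × months = 16 × 1500 × 6 = 144,000, an exact match. The implied cluster-period size is 1500 × 3 = 4,500. The article does not print this figure.

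**Step 2: use the counted weeks.** The only change is to the number of months.

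| Conversion | Weeks per month | Months in 24 weeks | Total | Per cluster-period | Below 144,000 by |
|---|---|---|---|---|---|
| 52-week year | 52/12 = 4.333 | 5.54 | 132,923 | 4,154 | 11,077 (7.7%) |
| 365.25-day year | 365.25/84 = 4.348 | 5.52 | 132,468 | 4,140 | 11,532 (8.0%) |

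Both conversions give roughly 133,000 in total and 4,150 per cluster-period.

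**Step 3: what would rescue 144,000.** A month of exactly 4 weeks makes 24 weeks equal to 6 months and returns 144,000. In calendar months that needs 144,000 / (16 × 5.5195) ≈ 1,631 patients per hospital per month, not 1500. Two 13-week windows would give about 143,500, but the design fixes 12 weeks.

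**Step 4: effect on power, nonadherence ignored.** The article does not print its formula, so a standard two-period cluster crossover approximation is assumed here.

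- Individually randomised size per condition for 0.16 versus 0.15 at 80% power: n = 20,559.
- Design effect: DE = 1 + (m − 1) × 0.006 − m × 0.006 × 0.95.
- Clusters required before corrections: n × DE / m.
- Variance of the difference with K clusters: (0.16 × 0.84 + 0.15 × 0.85) × DE / (m × K).

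| | m = 4,500 | m = 4,140 |
|---|---|---|
| DE | 2.344 | 2.236 |
| Clusters required | 20,559 × 2.344 / 4,500 = 10.7 | 20,559 × 2.236 / 4,140 = 11.1 |
| Power, 12 sites, normal approximation | 84.3% | 83.0% |
| Power, 16 sites, t with 14 df | 88.9% | 87.8% |

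The loss is 1.3 points at 12 sites and 1.1 points at 16. It is small because the design effect falls along with m: with an autocorrelation below 1, part of the variance does not shrink as more patients are added per cluster-period.

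**The case against.** The best defence is that the hospital is the unit that was randomised and sized. The section ends with 16 sites, and the patient total is a by-product labelled approximate. No stopping rule depends on it, and the analysis weights clusters equally. The 1500 is a 2013 average over all eligible hospitals, so actual volumes may differ in either direction. Six months may simply be shorthand for two periods of about three months.

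Most of this stands, and it limits the importance of the point. It does not make the figure right. The total is the exact product of the stated inputs with a duration that the design does not have, so it is not a rounded version of the 24-week result. The article nowhere defines a month as four weeks, and its rate comes from calendar-year data.

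The power figures above leave out nonadherence, which the article says it allowed for. They therefore do not reproduce the article's 12 sites. They show only how far power moves when m changes.

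A reader might go further in three ways that the documents do not support:

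- **That the true total is lower still, because 1500 includes admissions that are not index admissions.** Nothing in the article shows this. It speaks of patients, the eligibility filters may already be in the figure, and how the rate was counted is detail that a condensed article may leave to the full protocol. Any reduction would rest on an assumed readmission share.
- **That the eligible unit is ambiguous.** It is not. The eligibility section fixes it as the index admission, so the mismatch between abstract and Sample Size section is one of wording.
- **That the final report will look short of target.** This is conjecture, since it presumes that actual volumes equal the 2013 average and that readers treat an approximate figure as a target.

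**Conclusion.** The point holds as an arithmetic inconsistency in a stated design figure. At the article's own rate, its own inclusion windows give about 133,000 patients and about 4,150 per cluster-period. The stated 144,000 is too high by about 11,000, or 8%.

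This rests on two assumptions: that a month is a calendar month, and that the 1500 already refers to patients who count for the analysis. It is no evidence that the trial is underpowered. The change in power is about 1 percentage point under the approximation used, the required number of clusters stays below the stated 12 (10.7 against 11.1), and the 16 sites need not change.

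**What to change.** In the abstract and the Sample Size section, restate the anticipated size as about 133,000 patients with an index admission (16 sites, 24 counted weeks, assumed 1500 per hospital per month). Use that one unit in both places. Replace the six months in the power statement by two 12-week periods, and run the power calculation with about 4,150 patients per cluster-period. If the 1500 was in fact meant per four weeks, say so explicitly instead; the total of 144,000 then follows.

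The cost is wording and one rerun of the calculation. The stated size becomes slightly less favourable, while the design, the number of sites and the analysis stay as they are.

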#### Analysis Populations

Our primary analysis will use the intention-to-treat approach and will include all enrolled patients in the treatment groups to which their cluster was randomized at the time of the index hospitalization. Because true fluid exposure status is not recorded in administrative databases, all admitted patients will be included in the analysis, regardless of actual fluid administration.

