### Conclusions

We describe the protocol and statistical analysis plan for the evaluation of primary and secondary outcomes for the FLUID trial. FLUID will determine whether RL as compared with NS reduces death or requirement for hospital readmission by an absolute difference of 1%. In contrast to trials that have generated evidence in specific populations with fluid interventions limited to geographic locations in the hospital (ICU, ED), the results of FLUID will apply broadly to patients who are admitted throughout the hospital. As such, FLUID will provide important evidence-based guidance at the hospital and system level as to what fluids could be predominantly stocked for use throughout the hospital and the associated health care resources required for such supply.

The results of FLUID will help define clinical practice for physicians who care for patients admitted to the hospital regardless of whether differences between the 2 fluid groups in the proposed clinical outcomes are found. The question of the selection of optimal crystalloid fluid is, as evidenced by contemporaneous studies on this theme, an international one, and the results of FLUID will impact hospital management practices around the world. Should FLUID reveal a difference in clinical outcomes for patients, reflected in lives saved and hospital admissions avoided, then one fluid will become the dominant fluid stocked in centers; it may also result in significant savings to the health care system through bulk purchasing of one type of fluid. If no differences are found, then the less expensive crystalloid fluid may become the dominant fluid stocked in centers.

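### The sample size is said to allow for nonadherence, but its inputs give 12 sites only for an undiluted 1% difference, and the article does not say whether 1% is before or after nonadherence

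*Protocol article*

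**What the plan says.** All of the inputs are in the Sample Size section of the protocol article. The target is "80% power with a 2-sided α of 0.05" and a "minimum clinically important absolute difference of 1% in the primary outcome in favor of RL", "assuming a proportion of 0.16 in the NS condition". Clustering enters through "a within-period intracluster correlation coefficient of 0.006" and a cluster autocorrelation of 0.95, with 1500 patients per hospital per month. These are said to require 12 sites. The section then adds: "Our calculations account for nonadherence based on pilot data (94% adherence NS, 80% RL"). Two further sites are a small-sample correction and two are for variation in cluster size, which makes 16. No site is assigned to nonadherence, and no diluted or full-adherence difference is given.

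Three other places bear on the point:

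- Adherence and Protocol Deviations defines adherence as the allocated fluid's share of all saline and Ringer's lactate used, so nonadherent use is use of the other fluid.
- Analysis Populations sets an intention-to-treat analysis in which "all admitted patients will be included in the analysis, regardless of actual fluid administration".
- Conclusions says "FLUID will determine whether RL as compared with NS reduces death or requirement for hospital readmission by an absolute difference of 1" percent, without saying whether that is the effect of the fluid or of the stocking policy.

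**The concern.** A reader of the Sample Size section will take it that the trial has at least 80% power for a 1% effect after allowing for 6% crossover under saline and 20% under Ringer's lactate. Normally such an allowance either raises the number of clusters or is shown as a smaller difference to be detected. Here neither is visible: the difference stays at 1%, and the only additions to the 12 sites have other stated purposes.

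What is at stake is the effect for which the stated power holds. A 1% effect of the fluid and a 1% effect of a policy with imperfect uptake are different targets. At the stated adherence they differ by a factor of 0.74, and power differs materially between them.

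**Working it through.** **Inputs** (Sample Size section unless noted)
- Proportions: 0.16 under saline, 0.15 under Ringer's lactate.
- ρ = 0.006, cluster autocorrelation (CAC) = 0.95.
- Patients per cluster-period: m = 1500 × 3 = 4500, which agrees with 144,000 / (16 × 2) = 4500. Counting exactly 12 weeks instead gives 1500 × 12 × 12/52 = 4154.
- Two-sided 5% and 80% power: (1.960 + 0.842)² = 7.849.
- Reference distribution for the analysis: t on clusters minus 2 df, equal weight per cluster (Primary Analyses of the Primary and Secondary Outcomes).

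**Formula.** The variance of one cluster's between-period difference is V = 2σ²[(1 − ρ)/m + ρ(1 − CAC)], where σ² is the mean of p(1 − p) over the two arms. The number of clusters is K = 7.849 × V / d².

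**Step 1: reproduce the plan's 12 with no dilution**
- σ² = (0.1344 + 0.1275)/2 = 0.13095.
- V = 0.2619 × (0.000221 + 0.000300) = 1.364 × 10⁻⁴.
- K = 7.849 × 1.364 × 10⁻⁴ / 0.01² = 10.7, which is 11, or 12 as an even number for 1:1 sequences. With m = 4154, K = 11.1, which is 12 directly.
- Power at 12 sites, normal approximation: 84% (83% with m = 4154).

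The stated 12 is therefore obtained with the full 1% and no allowance for nonadherence.

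**Step 2: apply the stated adherence to a 1% full-adherence effect**, assuming the effect is linear in the share of fluid received
- Saline periods: 0.94 × 0.16 + 0.06 × 0.15 = 0.1594.
- Ringer's lactate periods: 0.80 × 0.15 + 0.20 × 0.16 = 0.1520.
- Difference: 0.0074, that is (0.94 + 0.80 − 1) = 0.74 of 1%.
- V = 1.369 × 10⁻⁴, so K = 7.849 × 1.369 × 10⁻⁴ / 0.0074² = 19.6, or 20 sites before any add-on (20.3 with m = 4154).

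**Step 3: power, like for like** (m = 4500, equal cluster sizes, no gain from covariate adjustment)

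| Intention-to-treat difference | Method | 12 sites | 16 sites |
|---|---|---|---|
| 0.74% | normal approximation | 59% | 72% |
| 0.74% | t, clusters − 2 df | 51% | 65% |
| 1% | normal approximation | 84% | 93% |
| 1% | t, clusters − 2 df | 76% | 89% |

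The article gives no coefficient of variation (CV) of cluster size. At an assumed CV of 0.6, which multiplies the 1/m term by 1 + 0.36, the t-based figures at 16 sites become 59% for 0.74% and 84% for 1%.

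**Step 4: can another reading of the inputs give 12 with dilution?**
- Counting only the Ringer's lactate nonadherence (factor 0.80): K = 16.8, so 17 sites.
- Rounding in the favourable direction (ρ = 0.0055, CAC = 0.955) with the 0.74 factor: K = 17.7.
- One-sided 5% test with the 0.74 factor: K = 15.5.
- CAC of 0.98 instead of 0.95, with the 0.74 factor: K = 12.8.

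None of these reaches 12.

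**Step 5: the other direction.** If 1% is the difference after nonadherence, the full-adherence effect it implies is 1% / 0.74 = 1.35%.

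**The case against.** The strongest reply is that 1% was always the net difference. The trial compares stocking policies, its estimand is a cluster-average effect meant to inform a health-system decision, and the analysis is by intention to treat. A 1% difference in the primary outcome between policies would naturally have nonadherence already inside it. Choosing a net difference with the expected adherence in mind is, in a loose sense, one way of accounting for it. On that reading 12 sites is right before the add-ons. This stands: nothing in the article says that 1% is a full-adherence effect, so a reader who infers that the trial simply has about 60% power goes further than the documents allow. What the reply does not supply is any trace of 94% and 80% in the calculation, or any statement of the larger effect from which a net 1% would have come.

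Two technical objections also stand in part. First, the planned covariate adjustment should improve precision by an amount the article does not give. If it cut the variance by 10 to 20% (an assumption), the t-based 65% would become about 70 to 75%, still below 80%. Second, the 59% at 16 sites depends on a CV that the article does not state, so it is an illustration only.

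Two stronger inferences should not be drawn. A reader might argue that admitted patients who receive neither fluid dilute the effect further. The article gives no figure for this, and the 16% and the 1% both refer to the outcome as analysed in all included admissions. A reader might also infer that a null result will be taken to exclude a 1% effect. The plan tests superiority and reports absolute differences with 95% confidence intervals, and no section says that non-significance rules out 1%.

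**Conclusion.** The point holds in a conditional form. The printed inputs give 12 sites only with an undiluted 1%, so the sentence on nonadherence does not describe how the site count was reached if 1% is a full-adherence effect. In that case about 20 sites were needed before the add-ons, and the 16 planned give at most about 65% power under the planned t distribution without adjustment. Even crediting all four extra sites to dilution under the normal approximation leaves 72%. If 1% is the net policy difference, the design is adequately sized, and the fault is that the paragraph claims an adjustment that did not affect the count and omits the implied 1.35%. The documents do not settle which reading is meant.

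Reproducing 12 without dilution rests only on printed figures. The 0.74 factor rests on linearity in fluid share and on nonadherent use being the other fluid, which follows from the article's own definition of adherence.

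**What to change.** Keep 16 sites and reword two places.

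1. In Sample Size, state whether 1% is before or after nonadherence.
   - If it is the net policy difference: say so, give the implied full-adherence effect of about 1.35% at 94% and 80% adherence, and put that explanation in place of the present nonadherence sentence. Power for 16 sites can then be given as about 89% (t on 14 df, equal cluster sizes), with the cluster-size CV used for any lower figure.
   - If it is the full-adherence effect: give the diluted difference of 0.74% and restate power for 16 sites as at most about 65% (t on 14 df, unadjusted).
2. In Conclusions, make the 1% refer explicitly to the net difference between stocking policies. If 1% proves to be the full-adherence effect, add the diluted net figure there.

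The cost is a few sentences and, on the second reading, a less favourable power statement. Outcomes, estimand, analysis and recruitment are unaffected.
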